### 2.8. Study Outcomes

There are two co-primary endpoints; maternal weight change between enrolment and 36 weeks’ gestation and neonatal birthweight. Neonatal sex-appropriate SD scores (SDS) will be calculated for weight and length measurements (with adjustments for gestational age at birth) using customised centiles (UK 1990 growth reference using LMS growth software LMSgrowth) [32].

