#### 2.6.3. Randomisation and Blinding

At the first visit, a unique participant number will be allocated by the recruitment team. Using the participant number, women will be randomly assigned to the energy restriction arm (1200 kcal/day) or the standard dietary arm (2000 kcal/day). This randomisation protocol was designed by a statistician based upon participant numbers and has been integrated within the online food ordering system. The allocation, therefore, is blinded from the participant, research team, and clinical teams, but is automatically available to the industrial partner for preparation of the diet box. This process is audited on a monthly basis to ensure the randomization is running smoothly for both arms of the study.

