### 2.9. Sample Size Justification

Retrospective data assessing the effect of late gestational weight gain (GWG) upon pregnancy outcomes were used to inform the sample size calculation [36]. The following sample size examples are based upon alpha 0.05 and power 0.9.

In the retrospective study, women had a standard deviation of 2 kg for late GWG and <3 kg for total GWG. Allowing for a standard deviation of 3 kg and a 1 kg difference between groups, 190 women per group will be required to give 90% power for the primary maternal endpoint.

The neonatal primary endpoint will be standardised birthweight. Recruitment of 175 women per group will give 90% power for identification of a 0.3 sd difference in standardised birthweight. As the standard deviation for birthweight was 508 g, this broadly equates to a difference in birthweight of 150 g.

A study size of 500 participants will provide sufficient statistical power and will allow for a 20–25% withdrawal rate. This sample size will also give sufficient power to detect secondary outcomes:To identify an increase in LGA (odds ratio (OR) 2.25 at 80% power).To identify a difference in maternal glycaemia at 36 weeks, for example, differences in mean CGM glucose (0.3 mmol/L difference), time in target (8% difference in time in target (3.5–7.8 mmol/L; >100 min per day), which has been associated with clinically relevant differences in neonatal outcomes) [8].To identify a 0.7 mmol/L difference in maternal postnatal two-hour OGTT glucose.

Several secondary analyses will be performed. A per protocol analysis will be performed in participants with >80% compliance and at least four weeks’ exposure to the intervention. Data will be used in a qualitative way to assess predictors for withdrawal or poor compliance. Consent will also be taken to collect and analyse outcomes for women who withdraw from the study, to allow assessment of reasons for withdrawal and their bearing upon outcomes.

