### 2.10. Statistical Analysis

An intention to treat analysis of the co-primary outcomes will be based on t-tests between trial arms and linear regression models with adjustment for baseline variables and the stratification variable of study centre using a fixed effects model. In addition, the model for maternal gestational weight change will be adjusted for baseline weight as an explanatory variable. The potential role of other explanatory variables such as pre-pregnancy BMI or information from the questionnaires will be investigated in sensitivity analyses. Secondary outcomes will be examined through regression analyses (linear or logistic) appropriate for the type of outcome being considered. A further secondary analysis will be performed to assess if main results are altered with addition of early GWG to the regression model. Safety analyses will be performed to assess any quantitative difference in effects, rates of small-for-gestational-age (SGA)/IUGR, stillbirth, neonatal hypoglycaemia, and admission to NICU.

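### Two co-primary endpoints are each sized at a full alpha of 0.05 with no allowance for there being two: an either-endpoint claim carries about 9–10% family-wise error, and a both-endpoints claim has joint power below the per-endpoint 90% in most scenarios

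*Protocol article*

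**What the plan says.** Section 2.8 of the protocol article names two primary outcomes of equal standing: "There are two co-primary endpoints; maternal weight change between enrolment and 36 weeks", and neonatal birthweight.

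Section 2.9 gives one set of error rates: "The following sample size examples are based upon alpha 0.05 and power 0.9". It applies them to each endpoint in turn. For the mother: "Allowing for a standard deviation of 3 kg and a 1 kg difference between groups, 190 women per group will be required". For the neonate: "Recruitment of 175 women per group will give 90% power for identification of a 0.3 sd difference in standardised birthweight". The total is then set: "A study size of 500 participants will provide sufficient statistical power and will allow for a 20–25% withdrawal rate".

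Section 2.10 gives the same analysis for both: "An intention to treat analysis of the co-primary outcomes will be based on t-tests between trial arms", together with adjusted linear regression.

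Nowhere does the article say whether success needs one endpoint or both, divide alpha between them, or give a power for the pair.

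**The concern.** With two primary endpoints, the trial's error rate and power depend on how the two results are combined. Testing each at 0.05 fits a rule that requires both, but then the power that matters is the chance of winning on both. A rule under which either suffices needs alpha to be shared. The sizing in Section 2.9 does neither: each endpoint has the whole 0.05 and its own power figure.

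The result most open to dispute is a split one, for example a significant difference in weight change and none in birthweight. That pattern is quite possible, because weight change is the better-powered endpoint unless birthweight is retained much more completely. Without a rule fixed in advance, a split result could be called positive or negative after the fact.

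**Working it through.** **Inputs.** From Section 2.9: alpha 0.05, power 0.90; maternal difference 1 kg with SD 3 kg (1/3 SD); neonatal difference 0.3 SD; 500 women; 20–25% withdrawal. Also from Section 2.9: an SD of 2 kg observed for late weight gain.

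Assumptions: equal allocation (read from the equal group sizes), two-sided tests (this reproduces the maternal figure), normal approximation, and a correlation ρ of 0 to 0.5 between the two test statistics (not given in the article).

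**1. The plan's own figures.** n per group = 2(z₀.₉₇₅ + z_power)²/δ².
- Maternal, 90%: 2 × (1.960 + 1.282)² / (1/3)² ≈ 189.1, so 190. This reproduces.
- Neonatal, 90%: 2 × (1.960 + 1.282)² / 0.3² ≈ 233.5, so 234, not 175. At 80%: 2 × (1.960 + 0.842)² / 0.3² ≈ 174.4, so 175. The stated size therefore gives 80% power. This is a separate error and is kept apart in step 4.

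**2. Either endpoint suffices, each tested at 0.05.** Under independence the family-wise error is 1 − 0.95² = 9.75%. From the bivariate normal it is 9.5% at ρ = 0.3 and 9.1% at ρ = 0.5.

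**3. Both endpoints required, each tested at 0.05.** The mean of each test statistic is δ√(n/2), and marginal power is Φ(δ√(n/2) − 1.960). Joint power is the bivariate normal probability that both exceed 1.960. Completers per group are 250 × 0.75 = 187.5 to 250 × 0.80 = 200. Example at 187.5 per group and ρ = 0: means 3.23 and 2.90, marginal powers 89.8% and 82.8%, joint 0.8975 × 0.8276 = 74.3%.

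| Weight / birthweight, n per group | Weight SD | Marginal power | Joint power, ρ 0–0.5 |
|---|---|---|---|
| 187.5 / 187.5 | 3 kg | 90% / 83% | 74–77% |
| 200 / 200 | 3 kg | 92% / 85% | 78–80% |
| 187.5 / 250 | 3 kg | 90% / 92% | 82–84% |
| 200 / 250 | 3 kg | 92% / 92% | 84–86% |
| 250 / 250 | 3 kg | 96% / 92% | 88–89% |
| 187.5 / 187.5 | 2 kg | >99% / 83% | 83% |
| 200 / 200 | 2 kg | >99% / 85% | 85% |
| 187.5 to 250 / 250 | 2 kg | >99% / 92% | 92% |

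**4. Separating out the 175-per-group error.** If each endpoint really had the 90% that Section 2.9 gives it, joint power under independence would be 0.9 × 0.9 = 81%. With 234 completers per group on both endpoints, enough for 90% on birthweight, joint power would be 86–87% at SD 3 kg. So having two endpoints lowers joint power without the arithmetic error; the error lowers it further.

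**5. Cost of Holm under an either-endpoint rule** (smaller p-value against 0.025; if significant, the other against 0.05), SD 3 kg, ρ 0–0.5, by simulation:

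| n per group | Weight change: unadjusted → Holm | Birthweight: unadjusted → Holm |
|---|---|---|
| 187.5 | 89.8% → 87.1–88.3% | 82.8% → 80.8–81.5% |
| 200 | 91.5% → 89.2–90.3% | 85.1% → 83.4–84.0% |

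The loss is about 1–3 points per endpoint, and the power to win on at least one is 91–97%. A plain Bonferroni split would leave 84–86% and 75–78%.

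**The case against.** - **A rule may exist elsewhere.** This is a condensed article, and a success rule is commonly left to the full protocol or SAP, neither of which is shown. That stands: the absence of a rule here is not itself an error. What the article does fix is the sizing, with a full 0.05 for each endpoint and no allowance for two.
- **No false statement is made about joint power.** The 90% figures are attached to one endpoint at a time and introduced as examples. That also stands. A reader might infer that the article promises 90% power for both endpoints together, or a family-wise alpha of 0.05. It states neither.
- **The two consequences exclude each other.** A reader might infer that the trial has both a 10% false-positive rate and low power. It cannot have both: the first needs an either-endpoint rule, the second a both-endpoints rule. Co-primary often means that both must succeed, in which case alpha is not inflated. The endpoints could also be read as separate questions about mother and infant, where the need for adjustment is debated.
- **74–80% is the pessimistic corner.** It removes 20–25% from birthweight, although Section 2.9 plans consent to collect outcomes after withdrawal. It uses the cautious 3 kg SD, although 2 kg was observed for late weight gain. It also contains the separate neonatal sizing error. All of this stands, and the full range is therefore given. With complete birthweight data and an SD of 2 kg, joint power passes 90%.

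**Conclusion.** The point holds in conditional form. The article names two co-primary endpoints, gives each the whole alpha of 0.05, and nowhere adjusts the sizing for having two.

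- **Either endpoint suffices:** family-wise error of about 9–10%, with 9.8% the value under independence and lower values under positive correlation.
- **Both required:** alpha is controlled. Joint power runs from 74% to 89% at SD 3 kg, depending on losses, and from about 83% to 92% at SD 2 kg. It falls short of 90% in every scenario at the 3 kg SD that the article uses for sizing.

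The documents do not support the stronger statement that the trial has a 10% false-positive rate, nor that its power is only 74–80%. The first assumes a rule the article does not state; the second assumes the heaviest losses, the larger SD, and a shortfall that belongs partly to the neonatal arithmetic. The correlation range of 0 to 0.5 is an assumption throughout, and covariate adjustment, which might raise power, is not counted.

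**What to change.** State, before unblinding, which rule applies, unless the full protocol or SAP already does; in that case report it wherever the sizing is described.

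- **Either endpoint suffices:** test the two with the Holm procedure at an overall two-sided 0.05, and restate power on that basis. At 187.5–200 per arm this is about 87–90% for weight change and 81–84% for birthweight.
- **Both required:** keep 0.05 for each, say so, and report the joint power with the assumed SD, losses on each endpoint and correlation.

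The documents do not settle which rule is meant, so the choice is the sponsor's. In either case, correct the neonatal figure (175 per group gives 80% power for 0.3 SD) so that the restated power rests on sound marginal values.

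The cost is a sentence in the analysis section and revised power figures, plus about 1–3 percentage points of power per endpoint if Holm is used. No endpoint, data collection or recruitment target has to change.

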## Abstract

Gestational diabetes mellitus (GDM) annually affects 35,000 pregnancies in the United Kingdom, causing suboptimal health outcomes to the mother and child. Obesity and excessive gestational weight gain are risk factors for GDM. The Institute of Medicine recommends weight targets for women that are overweight and obese, however, there are no clear guidelines for women with GDM. Observational data suggest that modest weight loss (0.6–2 kg) after 28 weeks may reduce risk of caesarean section, large-for-gestational-age (LGA), and maternal postnatal glycaemia. This protocol for a multicentre randomised double-blind controlled trial aims to identify if a fully controlled reduced energy diet in GDM pregnancy improves infant birthweight and reduces maternal weight gain (primary outcomes). A total of 500 women with GDM (National Institute of Health and Care Excellence (NICE) 2015 criteria) and body mass index (BMI) ≥25 kg/m^2^ will be randomised to receive a standard (2000 kcal/day) or reduced energy (1200 kcal/day) diet box containing all meals and snacks from 28 weeks to delivery. Women and caregivers will be blinded to the allocations. Food diaries, continuous glucose monitoring, and anthropometry will measure dietary compliance, glucose levels, and weight changes. Women will receive standard antenatal GDM management (insulin/metformin) according to NICE guidelines. The secondary endpoints include caesarean section rates, LGA, and maternal postnatal glucose concentrations.

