### 2.2. Participant Eligibility

Eligible pregnant women are identified following diagnosis of GDM at 20 to 30 + 6 weeks’ gestation using a standard clinical 75 g oral glucose tolerance test (OGTT) in accordance with the NICE glucose thresholds (fasting ≥5.6 mmol/L and ≥7.8 mmol/L at two hours) [9]. Eligible women require a pre-pregnancy BMI ≥25 kg/m^2^ (based on measured weight at booking, using validated scales), singleton pregnancy confirmed by ultrasound, and planned antenatal care at the same or another participating trial centre throughout pregnancy. Women will be recruited by research midwives, nurses, or by their physician/obstetrician. Study documentation will be provided in advance and women who wish to participate will be offered an appointment to discuss the study and consent to participate. All women will give their written informed consent before participation in any trial related activities.

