### 2.3. The Following Exclusion Criteria Will Be Applied

Women with evidence of multiple pregnancy or severe congenital abnormality on ultrasound; termination planned; pre-existing comorbidities such as renal failure, severe liver disease, cardiac failure, and psychiatric conditions requiring in-patient admission; medications at the time of the OGTT that may interfere with results (e.g., high dose steroids, immunosuppressants); complications such as preterm labour, severe anaemia, or intrauterine growth restriction (IUGR) at GDM diagnosis; haemoglobin A1c (HbA1c) at diagnosis of GDM of >48 mmol/mol; previous diabetes diagnosis; specialised dietary requirement (e.g., vegan or severe nut allergy); and weight loss >5% based between pre-pregnancy weight (weight first measured in pregnancy at booking) and 28 weeks’ gestation.

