### 2.5. Baseline Measurements and Randomisation

An outline of the protocol is detailed in Figure 1. Women who wish to participate and have given written informed consent are randomised before 30 + 6 weeks’ gestation.

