#### 2.5.1. Clinical Measures

At recruitment, baseline blood pressure and anthropometric measurements (including weight, height, waist, mid upper arm circumference (MUAC) and neck circumferences, and skinfold thickness (SFT)) will be assessed. Participants will be measured barefoot and in light clothing. Weight will be recorded to the nearest 100 g using a calibrated electronic scale (Seca Hammer Steindamm). Height will be assessed to the nearest 0.1 cm with a calibrated wall-mounted stadiometer (SECA 286; Seca, Birmingham, UK). Body mass index (BMI; in kg/m^2^) will be calculated as weight divided by square height. The circumferences will be measured to the nearest 0.1 cm with a nonstretchable fiber-glass tape (Chasmors Ltd., London, UK). Waist circumference will be defined as the midpoint between the lowest rib margin and the iliac crest; MUAC as the mid-point between the tip of the shoulder and the tip of the elbow (olecranon process and the acromium); and the neck circumference as the midway of the neck, between the midcervical spine and midanterior neck. The SFT will be performed on the left side of the body from multiple sites, including triceps, biceps, suprailiac, and subscapular using a calibrated Harpenden skinfold caliper (Baty International, UK). Blood pressure will be taken once seated using a calibrated automatic oscillometric sphygmomanometer (Dinamap, machine) and systolic and diastolic blood pressure will be recorded. Measurements will be performed by trained research staff, following standard protocols. Quality control workshops will be set up during the trial, where study team members will conduct measurements alongside expert examiners to reinforce the importance of standardised procedures and to assess inter- and intra-observer errors.

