### 2.7. Intervention Visits

Women are invited for a visit at 32 (visit 2) and 36 weeks (visit 3) gestation, using ±7 days for each visit. During visits 2 and 3, participants will be weighed, have blood pressure taken, a CGM sensor inserted, and asked to complete a three-day food diary while wearing the concurrent CGM during the next 7–10 days. At visit 2, women will be offered participant information leaflets about voluntary procedures around the time of the birth, specifically placental biopsy, cord blood collection, and infant anthropometry measures to be taken at birth and six weeks postnatal. These procedures will be discussed again at visit 3, when specific consent for these additional voluntary procedures will be sought. Visit 3 will include completing all the questionnaires, maternal blood measures, and maternal anthropometry performed in visit 1.

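### The maternal co-primary endpoint starts at an enrolment with no stated lower gestational limit, and gestation is not a named covariate in its analysis

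*Protocol article*

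**What the plan says.** All references are to the protocol article.

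- **Endpoint (section 2.8).** One of the two co-primary endpoints is "maternal weight change between enrolment and 36 weeks" of gestation.
- **Start of the interval.** The baseline weight belongs to the recruitment visit (section 2.5.1: "At recruitment, baseline blood pressure and anthropometric measurements").
- **Who can enter, and when.** Section 2.2: "Eligible pregnant women are identified following diagnosis of GDM at 20 to 30 + 6 weeks". Section 2.5: women who "have given written informed consent are randomised before 30 + 6 weeks". No earliest gestation is given for enrolment or randomisation.
- **Start of the intervention.** The Abstract describes a "diet box containing all meals and snacks from 28 weeks to delivery". Section 2.1 describes the diet as covering the final 8 to 10 weeks of pregnancy.
- **End of the interval (section 2.7).** The 32- and 36-week visits are held "using ±7 days for each visit".
- **Analysis (section 2.10).** Both co-primary outcomes are analysed by intention to treat, with t-tests and linear regressions that adjust for centre and for baseline variables that are not listed. In addition, "the model for maternal gestational weight change will be adjusted for baseline weight as an explanatory variable". The text does not say whether the t-test or the regression is the primary result.
- **A related exclusion (section 2.3).** Women are excluded for "weight loss >5% based between pre-pregnancy weight (weight first measured in pregnancy at booking) and 28 weeks" of gestation.

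**The concern.** Weight changes with time in pregnancy, so a change score measured over unequal periods partly reflects how long each woman was observed. Here the starting point is an administrative event, enrolment, and not a fixed gestation or the first box. Women who enter early may contribute weeks in which neither arm has received anything. Women who enter late contribute a short period with less exposure to the diet.

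A t-test cannot allow for this, and the regression allows for it only if gestation happens to be among the unlisted baseline variables. At stake are the precision of a co-primary endpoint and the clarity of what the estimated difference refers to.

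The same open lower limit affects eligibility. Loss of weight up to 28 weeks cannot be known when a woman is randomised before 28 weeks, so section 2.3 and section 2.5 do not fit together for such a woman.

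**Working it through.** **1. The plan's own figure.** Section 2.9 gives an SD of 3 kg, a difference of 1 kg, alpha 0.05 and power 0.9. Two-sided testing is assumed because the text does not state it.

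n per group = 2 × (1.960 + 1.282)² × 3² / 1² = 189.1, rounded up to **190**, as stated. Power at 190 is 90.1%. A one-sided test would need 155, so the stated figure is two-sided.

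**2. Length of the interval.**

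| Reading | Shortest | Longest |
|---|---|---|
| Nobody enrols before 28+0, visit window used | 35+0 − 30+6 = 4.1 weeks | 37+0 − 28+0 = 9 weeks |
| Enrolment as early as 20+0, weighing exactly at 36+0 | 36+0 − 30+6 = 5.1 weeks | 36+0 − 20+0 = 16 weeks |
| Enrolment as early as 20+0, visit window used | 4.1 weeks | 37+0 − 20+0 = 17 weeks |

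On the last two readings up to 28 − 20 = 8 weeks come before the boxes. Even the narrowest reading has more than a twofold spread.

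**3. Added variance.** These assumptions are not in the document: weight gain of 0.2 to 0.5 kg/week, enrolment spread uniformly from a lower limit L to 30+6 (30.86 weeks), the 36-week weighing spread uniformly over 35 to 37 weeks, and an arm difference that stays at 1 kg.

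- SD of interval = √[(30.86 − L)²/12 + 2²/12]
- Total SD = √[SD² + (rate × SD of interval)²]
- Power = Φ(1 / (total SD × √(2/190)) − 1.960)

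For L = 20 the SD of the interval is √(9.82 + 0.33) = 3.19 weeks. At 0.5 kg/week this adds 1.59 kg, and √(9 + 2.54) = 3.40 kg.

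| Lower limit L | SD of interval | Starting SD | Total SD | n per arm for 90% | Power at 190 per arm |
|---|---|---|---|---|---|
| 20 weeks | 3.19 weeks | 3 kg | 3.07–3.40 kg | 198–243 | 88.8–81.8% |
| 24 weeks | 2.06 weeks | 3 kg | 3.03–3.17 kg | 193–212 | 89.6–86.7% |
| 28 weeks | 1.01 weeks | 3 kg | 3.01–3.04 kg | 190–195 | 90.0–89.3% |
| 20 weeks | 3.19 weeks | 2 kg | 2.10–2.56 kg | 93–138 | 99.6–96.8% |

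Each range runs from 0.2 to 0.5 kg/week.

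**4. What adjustment recovers.** Under the same assumptions, gestation at baseline accounts for the enrolment part of the variance. For L = 20 that is 9.82 of 10.16 weeks². What remains is the visit window: √0.33 = 0.58 weeks, times 0.5 kg/week = 0.29 kg. Then √(9 + 0.083) = 3.01 kg and power at 190 per arm is 89.9%. Nearly all of the loss is recovered.

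**The case against.** The case on the other side is substantial, and several stronger readings that a reader might infer are not supported.

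- **That women are enrolled from 20 weeks.** The range of 20 to 30+6 weeks is the window for diagnosis, not enrolment. The 28-week start of the boxes, the 8-to-10-week diet and the 28-week exclusion all suggest entry near 28 weeks. This stands: 17 weeks is only the widest reading that the text permits. But no section states a lower limit, and the Introduction puts usual diagnosis at 24 to 28 weeks, so entry before 28 weeks cannot be ruled out.
- **That gestation is left out of the model.** The baseline variables are unlisted and could include it, and a covariate list may properly sit in an analysis plan that is not shown. This stands, so the claim is only that the article does not name it. The t-test, which the article does name, cannot include it.
- **That the arms are biased.** Randomisation balances interval length in expectation, and the t-test remains valid. This stands in full.
- **That the trial is underpowered.** Section 2.9 reports SDs of 2 kg for late gain and below 3 kg for total gain, then plans on 3 kg. The plan therefore did not rest on the late-gain SD alone, and its margin may absorb the extra variance. This stands: the lowest power figures are a worst case.
- **That randomised women will be removed for losing weight.** No section says so, and section 2.10 specifies intention to treat. It is only a possible consequence of reading sections 2.3 and 2.5 together.

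**Conclusion.** The point holds in a limited form. The maternal co-primary interval has no defined starting gestation. It varies from about 4 to 9 weeks at the least and up to 17 weeks on the widest reading, and the article names no covariate that accounts for this. The result is extra variance, and so a smaller difference relative to its noise, together with an estimate that mixes different lengths of observation and exposure. It is not a bias between arms.

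The size depends on enrolment practice and the true SD, neither of which the document settles. With uniform enrolment from 20 weeks and a gain of 0.2 to 0.5 kg/week, power at 190 per arm is about 82 to 89% from a 3 kg SD and at least 96% from a 2 kg SD. With enrolment confined to 28 to 30+6 weeks it is 89 to 90%. The change is worth making because it costs almost nothing and protects precision in every scenario, not because the trial is shown to be underpowered.

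**What to change.** 1. Make the adjusted linear regression the primary analysis of maternal weight change, and keep the t-test as supportive. Name the covariates: baseline weight, centre and gestational age at the baseline weighing.
2. Name the interval to the 36-week weighing as well, and say whether it is planned or actual. The planned interval is simply 36 weeks minus gestation at baseline, so it adds nothing to that covariate. The actual interval also captures the visit window. It is known only after randomisation, so its use relies on blinding to keep visit timing unrelated to arm.
3. Keep the recruitment weight, taken before randomisation, as baseline. A weight at first box might look more natural, but it could be a post-randomisation value, might come from the loaned home scales, and would be missing for women who withdraw before their first box.
4. State the gestational range for enrolment and for the baseline weighing.
5. Reconcile the section 2.3 weight-loss exclusion with the section 2.5 timing of randomisation, so that eligibility is settled before randomisation and no randomised woman is removed from the intention-to-treat analysis.

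The cost is a few lines of analysis and eligibility text. It needs no new visit or measurement, only the gestation at each weighing, which the trial already needs in order to schedule its visits.
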